## **11.8.2. Statistical Analysis Methods**

### **11.8.2.1. General principles**

---

Measurement data will be described statistically with mean, median, standard deviation, maximum value, and minimum value; counting data or grade data will be expressed with frequency.

All statistical analysis will be performed using the statistical software SAS EG 8.3.

#### **11.8.2.2. Subject distribution, demographic information, and baseline characteristics**

The study screening, the number of subjects enrolled in each group, the number of subjects who completed the study, and the number of cases in each analysis set were summarized, and the dropout subjects and reasons for dropout were analyzed. The demographic characteristics of the subjects in each group were statistically described.

#### **11.8.2.3. Protection effectiveness analysis**

The person-year incidence rates and 95% confidence interval(CI) of COVID-19 confirmed by the central laboratory with clinical symptoms will be calculated among the test group and the control group 14 days after the vaccination, and the Poisson regression model will be used to analyze the statistical differences between the groups. VE and 95% CI based on the person-year incidence rates will be estimated with the model. The Poisson regression model takes the number of patients as the dependent variable, grouping as the fixed effect, and the exposure person-years of the participants as the offset, using the log connection function.

Person-year incidence rate=(number of cases)/(exposure person-years of the participants)×100%. In the calculation of the exposure person-years, the starting time is the 14th day after the vaccination, and the ending time is the day when a COVID-19 case was first confirmed. If the RT-PCR or antigen test was positive but not confirmed as a COVID-19 case, the person-year incidence rate was calculated using the RT-PCR or antigen test date as the termination time. VE rate=1- (person-year incidence rate of the test group)/(person-year incidence rate of the control group).

---

The VE will be evaluated in the prevention of clinically symptomatic COVID-19 confirmed by central laboratory virology 14 days after vaccination based on the sets of E-mFAS and E-PPS. The evaluation of VE based on E-mFAS is the main analysis result of this study.

In addition, the VE of the vaccine against clinically symptomatic COVID-19 confirmed by central laboratory virology 7 days after vaccination will be evaluated based on E-mFAS, and the statistical method is the same as the primary efficacy endpoint.

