### **6.2.3. Exploratory endpoint(s)**

➤ Exploratory endpoint(s) of protective efficacy

1)The person-year incidence rate of symptomatic COVID-19 cases of any severity (Appendix 1) occurring from 7 days after booster vaccination of the investigational vaccine or placebo in the adults aged 18 and older who have completed 2 or 3 doses of inactivated COVID-19 vaccines.

➤ Exploratory endpoint(s) of immunogenicity

1)The specific cellular immune response detected via cytokines IL-2, IL-4, IL-13, IFN- $\gamma$  (ELISpot) among the immunogenicity subgroup 7 days, 14 days, 28 days, and 3 months after booster vaccination of the investigational vaccine or placebo.

2)The correlation coefficient between neutralizing antibody, S-protein IgG antibody, and/or cellular immunity and vaccine protective efficacy after vaccination.

---

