## **11.8. Statistical analysis**

### **11.8.1. Analysis Sets**

#### **➤ Analysis set of efficacy**

**Full analysis set of efficacy(E-FAS):** Include all subjects who followed the intention-to-treat (ITT) principle, entered randomization and completed vaccination, and had at least one case surveillance follow-up after vaccination.

**Modified full analysis set of efficacy(E-mFAS):** It is a subset of E-FAS and includes all subjects who completed vaccination, had negative baseline nucleic acid results, and had at least 1 case surveillance follow-up 14 days after vaccination. Among them, COVID-19 cases with positive nucleic acid or antigen test or confirmed diagnosis within 14 days from enrollment to vaccination will also be excluded from this analysis set.

**Per protocol set of efficacy(E-PPS):** It is a subset of E-mFAS, including all subjects who did not violate the inclusion/exclusion criteria, completed vaccination, had negative baseline nucleic acid results, and had at least one case surveillance follow-up 14 days after vaccination, and did not violate the protocol. Among them, COVID-19 cases with positive nucleic acid or antigen test or confirmed diagnosis within 14 days from enrollment to vaccination will also be excluded from this analysis set.

Cases of E-mFAS and E-PPS are counted from 14 days after vaccination and are

---

mainly used for the evaluation of the main protective efficacy of the vaccine. Among them, E-mFAS is the main analysis set for the evaluation of protective efficacy in this study. E-FAS was used to evaluate the protective efficacy after vaccination.

➤ **Analysis set of immunogenicity**

**Full analysis set of immunogenicity(I-FAS):** Include all subjects in the immunization subgroup who follow the ITT principle, enter randomization and complete vaccination, and have valid antibody data before vaccination.

**Per protocol set of immunogenicity(I-PPS):** Include all subjects in the immunization subgroup who did not violate the inclusion/exclusion criteria, completed the vaccination, had blood samples collected at the evaluation time points, and had valid antibody data. The immunogenicity analysis sets were defined for the immunogenicity evaluation of each group at 7 days, 14 days, and 28 days after vaccination respectively.

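### The exploratory VE from day 7 is assigned to E-mFAS, which as defined holds no day 7–13 case, so the analysis repeats the day-14 result

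*Protocol*

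**What the plan says.** The exploratory efficacy endpoint in Protocol 6.2.3 (also in the synopsis) is "The person-year incidence rate of symptomatic COVID-19 cases of any severity (Appendix 1) occurring from 7 days after booster vaccination".

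Section 11.8.2.3 assigns its analysis: VE against disease "confirmed by central laboratory virology 7 days after vaccination will be evaluated based on E-mFAS". For the model and estimator it points back to the main analysis: "the statistical method is the same as the primary efficacy endpoint". The only rule for exposure person-years in that section starts the clock on the 14th day after vaccination and stops it when a case is first confirmed.

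Section 11.8.1 builds E-mFAS around day 14:
- participants must have "had at least 1 case surveillance follow-up 14 days after vaccination";
- "COVID-19 cases with positive nucleic acid or antigen test or confirmed diagnosis within 14 days from enrollment to vaccination will also be excluded";
- "Cases of E-mFAS and E-PPS are counted from 14 days after vaccination".

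The same section gives E-FAS the role of evaluating efficacy after vaccination. E-FAS has no early-positive exclusion and no day-14 counting start. Section 11.8.2.3 does not mention E-FAS.

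**The concern.** The endpoint starts on day 7, but the set chosen for it starts on day 14. The difference between the two endpoints is exactly the cases of days 7–13, and these are what the set leaves out. The result would carry a day-7 label but could not differ from the primary result because of anything that happened in that week.

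At stake is the exploratory question of how early protection begins. Sections 6.6 and 11.3 start twice-weekly monitoring on day 7, so the trial collects the relevant cases and then drops them from the one analysis meant to use them.

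A related wording fault lies in the exclusion sentence. Its window runs from enrolment to vaccination, yet the schedule of activities places both at Visit 1, Day 0. The sentence also defines the primary analysis set, so it deserves a clear rewrite in any case.

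**Working it through.** **Step 1: follow one participant.** Take a participant with symptoms and a positive test on day 10.

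| Rule | Place | Effect on the day-10 case |
|---|---|---|
| Endpoint counts from day 7 | 6.2.3 | Should count |
| Early positives excluded (natural reading: enrolment to 14 days after vaccination) | 11.8.1 | Participant leaves E-mFAS |
| Cases counted from day 14 | 11.8.1 | Not counted, even if the participant stayed in |
| Person-time runs from day 14 to first confirmation | 11.8.2.3 | End date falls before the start date |

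The expected number of day 7–13 cases in the named analysis is therefore 0 in both arms. With cases and person-time both starting on day 14, the day-7 VE equals the day-14 VE. The day-14 follow-up requirement adds little, because a participant positive on day 10 continues to be visited and can have a contact after day 14.

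**Step 2: reproduce the plan's figures.** Inputs from Protocol 6.5.1 are placebo incidence 9%, VE 60%, 1:1 allocation and 162 cases.
- Vaccine-arm risk: 0.09 × (1 − 0.60) = 0.036.
- Participants per arm: 162 / (0.09 + 0.036) = 1,285.7, so 1,286, as stated.
- Cases from day 14: placebo 1,286 × 0.09 = 115.7; vaccine 1,286 × 0.036 = 46.3; total 162.
- VE from day 14: 1 − 46.3/115.7 = 60%.

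**Step 3: illustrate the size.** The protocol gives neither the period over which the 9% accrues nor the VE in days 7–13. Both are assumed here. VE is approximated by the ratio of case counts in equal arms.

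With accrual spread evenly over days 14–180 (166 days), placebo cases in days 7–13 are 115.7 × 7/166 = 4.9.

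| Assumed placebo cases, days 7–13 | Early VE | VE from day 7 if these cases are kept | VE in E-mFAS as written |
|---|---|---|---|
| 4.9 | 0% | 1 − (46.3 + 4.9)/(115.7 + 4.9) = 57.6% | 60% |
| 4.9 | 90% | 1 − (46.3 + 0.5)/(115.7 + 4.9) = 61.2% | 60% |
| 23.1 (20% of later placebo cases) | 0% | 1 − (46.3 + 23.1)/(115.7 + 23.1) = 50.0% | 60% |

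Using an exponential constant hazard, 1,286 × [1 − exp(−7λ)] with λ = −ln(0.91)/166 gives 5.1 placebo cases, and VE of 57.5% and 61.3% for early VE of 0% and 90%. If the 9% accrues by day 90 instead (λ = −ln(0.91)/76), there are 11.1 placebo cases, and VE is 54.7% and 62.6%.

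The discrepancy can go either way. It vanishes when early VE equals later VE.

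**The case against.** **The endpoint is exploratory.** It carries no alpha, power or success criterion. The hypothesis in 6.4, the 162 cases and the main E-mFAS analysis are untouched. This stands in full and sets the severity.

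**E-FAS already exists for efficacy after vaccination.** This also stands in part. A reader might infer that the early-protection question cannot be answered at all, and the documents do not support that: a set that keeps early cases is defined and the data are collected. What remains is that 11.8.2.3 names a different set for this analysis.

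**The text is less strict than it looks.** The exclusion sentence is garbled, and the counting rule sits in a sentence saying that these sets mainly serve the main efficacy evaluation, so it could be read as describing the primary analysis only. But keeping a day-10 case needs both charitable readings at once, and the only stated person-time start would still be day 14.

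**Immortal time.** A reader might infer that each participant gains seven event-free days. That requires person-time to start on day 7 while cases start on day 14, and the protocol states no day-7 start. Even then both arms would gain the same seven days per participant, and VE would hardly move.

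**The size is modest.** With even accrual and no early protection the gap is 60 − 57.6 = 2.4 points on an unpowered estimate. The 50% figure needs both a front-loaded wave and zero early VE, neither of which is in the protocol.

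**Conclusion.** The point holds, limited to an exploratory endpoint. As written, the from-day-7 VE uses a set and a counting rule that leave out every day 7–13 case, so it reproduces the day-14 VE. This follows from the definitions, on the natural reading of the exclusion window, and does not depend on any assumed rate. It is a stated rule that gives the wrong quantity, rather than detail left to the SAP.

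The numerical size does rest on assumptions. With even accrual over days 14–180, the from-day-7 VE would be about 57.6% to 61% for early VE between 0% and 90%, against 60% reported. Larger gaps need faster or front-loaded accrual. The inference that the primary result, the event target or type I error is compromised is not supported. The change should be made, but it is not critical.

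**What to change.** In 11.8.2.3, run the day-7 VE in E-FAS restricted to participants with a negative baseline nucleic acid result, no positive test or diagnosis before day 7, and at least one surveillance contact from day 7. State that case counting and person-time both start on day 7.

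In 11.8.1, reword the E-mFAS and E-PPS exclusion window as *from enrolment through day 13 after vaccination*.

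The cost is two sentences, best settled before unblinding. Monitoring already starts on day 7, so no new data are needed, and the sample size does not change.

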#### **11.8.2.4. Immunogenicity analysis**

The positive conversion rates of SARS-CoV-2 neutralizing antibodies in the test group and the control group will be calculated respectively in the immunization subgroup, and the Clopper-Pearson method will be used to calculate the 95% CI. The chi-square test/Fisher's precision probability test will be used to compare the statistical differences in the positive conversion rates between the test group and the control group.

The GMT and GMI of SARS-CoV-2 neutralizing antibodies in the test group and the control group in the immunogenicity subgroup will be statistically described with geometric mean and two-sided 95% CI. The paired t-test of the logarithmically transformed results will be used to perform statistical tests on the difference between the test group and the control group.

The degree inverse distribution graph of the antibody titers of anti-SARS-CoV-2 neutralizing antibody and IgG antibody in the test group and control group in the immunogenicity subgroup will be plotted before immunization and 7 days, 14 days, 28 days, 3 months, and 6 months after the vaccination.

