### 6.5.2. Sample Size Allocation

This study plans to enroll approximately 3,200 participants who have completed 2 or 3 doses of inactivated COVID-19 vaccine for  $\geq 6$  months (Study No. 0001~3200). All participants with informed consent, physical examination, and screening will be 1:1 randomly assigned into the experimental group or the control group (1,600 participants in each group) and followed up for safety and protective efficacy.

In this study, the first 50 participants enrolled in each group (a total of 100 participants) will be set as the immunogenicity subgroup (Study No. 0001~0100). All participants enrolled need to be followed up for safety and protective efficacy after vaccination. The participants in the immunogenicity subgroup also need to collect blood for the detection of immunogenicity-related indicators before vaccination and 7 days, 14 days, 28 days, 3 months, and 6 months after vaccination. Extra blood will be collected for cellular immunity test before vaccination and at days 7, 14, 28, and month 3 after vaccination.

The groups, vaccines, and planned sample size are detailed in the table below:

| Participants                           | Groups        | Vaccines | Immunogenicity subgroup | Non-immunogenicity subgroup | Sample size(no.) |
|----------------------------------------|---------------|----------|-------------------------|-----------------------------|------------------|
| Adults aged 18 and older who have been | Study group   | LVRNA012 | 50                      | 1550                        | 1,600            |
|                                        | Control group | Placebo  | 50                      | 1550                        | 1,600            |

---

|                                                                                                  |       |     |      |       |
|--------------------------------------------------------------------------------------------------|-------|-----|------|-------|
| inoculated with 2 or 3

doses of inactivated

COVID-19 vaccines for

≥6 months | Total | 100 | 3100 | 3,200 |
|--------------------------------------------------------------------------------------------------|-------|-----|------|-------|

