### **7. Study population**

#### **7.1. Inclusion criteria**

Participants must meet all the following inclusion criteria:

- (1) Both male and female adults aged 18 years and above who can provide their identification;
- (2) Understand the contents of the ICF and the vaccine for this vaccination, sign the ICF, and have the ability to use a thermometer, scale, and fill in the diary card and contact card as required;
- (3) Be able to communicate well with the researcher and understand and comply with

---

the requirements of this study;

(4) Participants must have received 2 or 3 doses of SARS-CoV-2 inactivated vaccine, with the last dose received at least 6 months before enrolment.

(5) Healthy participants or participants with mild underlying disease [in a stable state without exacerbation (no admission to hospital or no major adjustment to treatment regimen, etc.) for at least 3 months before enrollment in this study].

(6) For female participants: without childbearing potential (amenorrhea for at least 1 year or documented surgical sterilization) or not in pregnancy or lactation and have used effective contraception (e.g., intrauterine or implantable contraceptive devices, oral contraceptives, injectable or buried contraceptives, sustained-release topical contraceptives, intrauterine devices (IUDs), condoms (for males), diaphragms, cervical caps, etc.) for the past 14 days before the first dose of vaccine (provide negative pregnancy certificate within 48 hours);

(7) Negative results within 48 hours for SARS-CoV-2 pathogenicity testing (RT-PCR).

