#### **11.5. Immunogenicity observation method**

Participants in the immunity subgroup: about 5.0 mL of venous blood will be collected and placed in a procoagulant tube (containing only procoagulant) before vaccination, 7 days, 14 days, 28 days, 3 months, and 6 months after vaccination for detection of live virus neutralizing antibody and specific IgG antibody of current epidemic strain.

Participants in the immunity subgroup: An additional 15mL venous blood will be

---

collected before vaccination, 7 days, 14 days, 28 days, and 3 months after vaccination to detect IL-2, IL-4, IL-13, and IFN- $\gamma$  cytokine levels (ELISpot method).

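### The between-arm comparison of post-dose neutralizing GMT is not adjusted for the day-0 titre; it is valid, but less precise than the data already collected allow

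*Protocol*

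**What the plan says.** Section 6.5.2 sets up the immunogenicity subgroup: "the first 50 participants enrolled in each group (a total of 100 participants) will be set as the immunogenicity subgroup". These participants are to "collect blood for the detection of immunogenicity-related indicators before vaccination", and again at 7, 14 and 28 days and at 3 and 6 months. Section 11.5 repeats the pre-dose draw. Section 11.8.1 admits to I-FAS only subgroup members who "have valid antibody data before vaccination".

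Section 11.8.2.4 then gives the analysis. Neutralizing GMT and GMI by arm "in the immunogenicity subgroup will be statistically described with geometric mean and two-sided 95% CI". The test comes next: "The paired t-test of the logarithmically transformed results will be used to perform statistical tests". It is applied between the two arms. SCR is compared by chi-square or Fisher's exact test. The section mentions no baseline covariate and no adjusted GMT ratio. For S-protein IgG it names only a distribution graph, although section 6.2.2 lists GMT, GMI and SCR for IgG as secondary endpoints too.

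Two of the three neutralizing-antibody measures are defined against day 0. GMI is the geometric mean increase, and the synopsis defines SCR by a four-fold rise over the pre-immunization titre (or over the detection limit when the pre-dose value is below it).

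**The concern.** Baseline titres in this population should vary. Section 7.1 states "Participants must have received 2 or 3 doses of SARS-CoV-2 inactivated vaccine", with the last dose at least 6 months earlier and no upper limit on the interval. Exclusion criterion 2 in section 7.2 bars COVID-19 only within the last 6 months. Criterion 3 also lists other coronavirus infections at any time. If that were read to cover COVID-19, earlier infection would drop out as a source of variation, but number of doses and interval would remain.

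With 50 per arm, the arms can differ at day 0 by chance. A post-dose GMT ratio that ignores day 0 inherits part of that difference and keeps variance that the day-0 titre could explain. At stake is the precision of a secondary endpoint that rests on 100 people. The protocol names the test itself, so the method is fixed here and not merely left to the SAP.

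**Working it through.** **Inputs.** From the protocol: n = 50 per arm, 1:1 allocation, a day-0 titre on everyone in I-FAS. Not in the protocol, so assumed: SD of log10 titre of 0.5 (range 0.4 to 0.6), equal before and after the dose, and pre/post correlation r of 0.2 to 0.7.

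**The plan's own figure.** There is none to reproduce: no power, SD or precision is stated for the subgroup. The only sizing, in section 6.5.1, is for efficacy (1,286 × 0.09 × 1.4 = 162.04, matching the 162 cases). It plays no part here.

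**Formulas.** Variance of the between-arm difference in mean log10 titre:

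- post-dose only (GMT ratio): 2·SD²/n
- change from day 0 (GMI ratio): 2·SD²/n × 2(1 − r)
- adjusted for day 0 as a covariate: 2·SD²/n × (1 − r²), ignoring the small cost of estimating the slope

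**Relative variance and sample-size equivalent.** The reduction against GMT is r². Adjusted divided by GMI is (1 + r)/2, which is below 1 for every r below 1.

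| r | GMT | GMI | Adjusted | Cut vs GMT | Cut vs GMI | 50 per arm acts like |
|---|---|---|---|---|---|---|
| 0.2 | 1 | 1.60 | 0.96 | 4% | 40% | 50/0.96 = 52 |
| 0.3 | 1 | 1.40 | 0.91 | 9% | 35% | 50/0.91 = 55 |
| 0.5 | 1 | 1.00 | 0.75 | 25% | 25% | 50/0.75 = 67 |
| 0.7 | 1 | 0.60 | 0.51 | 49% | 15% | 50/0.51 = 98 |

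GMI is thus less precise than raw GMT when r is below 0.5, and is never more precise than the adjusted comparison.

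**On the titre scale, SD 0.5.** The unadjusted SE is 0.5 × √(2/50) = 0.10 log10, so the 95% CI multiplies and divides the GMT ratio by 10^(1.96 × 0.10) = 1.57. With adjustment the factor is 10^(1.96 × 0.10 × √(1 − r²)):

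| r | 95% CI factor | Ratio detectable with 90% power |
|---|---|---|
| unadjusted | 1.57 | 2.11 |
| 0.2 | 1.56 | 2.08 |
| 0.3 | 1.54 | 2.04 |
| 0.5 | 1.48 | 1.91 |
| 0.7 | 1.38 | 1.70 |

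**Chance baseline imbalance.** The day-0 difference between arms has the same SE of 0.10 at SD 0.5, so its 95% range reaches 1.57-fold either way (1.43-fold at SD 0.4, 1.72-fold at SD 0.6). Given a day-0 difference d on the log scale, the GMT comparison is shifted by r·d and the GMI comparison by −(1 − r)·d. The adjusted comparison is not shifted. At r = 0.5 and d = 0.196 (the 1.57-fold case), the GMT ratio is pushed by 10^0.098 = 1.25-fold one way and the GMI ratio by as much the other way.

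**The case against.** The strongest reply is that nothing here is wrong. Unadjusted GMT, GMI and SCR are unbiased under randomization and match the three endpoints listed in section 6.2.2. No immunogenicity hypothesis, margin or power is stated, and an adjusted supplementary estimate could sit in the SAP. That the comparison is valid stands. The SAP argument stands only in part, because section 11.8.2.4 itself names the between-arm test.

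The size is also open to challenge. SD and r are assumed. A saline arm should track its baseline more closely than a boosted arm, so a common r and equal variances may fail, and many day-0 values below the detection limit would shrink the gain. The background in section 2 cites 5- to 10-fold and 27-fold antibody increases after mRNA boosting. Those studies used other comparators, but effects of that order would show clearly without adjustment. These points limit the benefit without removing it.

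Three stronger readings are tempting, and the protocol does not support them:

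- **That day 0 is ignored altogether.** GMI and SCR, compared in the same section, both refer to it.
- **That GMT and GMI give rival answers of which one must be wrong.** They are separate declared endpoints. The opposite shifts shown above arise only conditional on a chance imbalance; over randomization both comparisons are unbiased.
- **That adjustment costs no participants anywhere.** That follows for I-FAS. The definitions of I-PPS and of IPS, which serves the 3- and 6-month results, do not explicitly require a pre-dose titre.

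**Conclusion.** The point holds as a matter of efficiency, not validity. Section 11.8.2.4 fixes an unadjusted between-arm comparison of neutralizing GMT although a day-0 titre is in hand, and neither GMI nor SCR recovers the full precision. The gain from adjustment runs from negligible (4% of variance at r = 0.2) to substantial (49% at r = 0.7), given equal variances and a common correlation that the protocol does not state. It concerns a secondary endpoint in a subgroup with no stated power. The primary efficacy result does not depend on it. This is a worthwhile improvement, not an error that threatens a conclusion.

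**What to change.** In section 11.8.2.4, replace the t-test sentence. At each post-dose time point, fit a linear model of log10 titre on arm and log10 day-0 titre, and report the back-transformed adjusted vaccine/placebo GMT ratio with its 95% CI as the between-arm result. Do the same for S-protein IgG. Keep observed GMT, GMI and SCR by arm. State one rule for titres below the detection limit, the same in both arms and at day 0.

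The sentence needs rewriting in any case, because it names a paired test for two independently randomized arms. A plain two-sample t-test would cure that fault but leave this one; the model settles both.

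The cost is one model statement, with no new samples, visits or assays. Nobody leaves I-FAS. In I-PPS and IPS, any participant without a valid pre-dose titre would drop out of the adjusted model. This is a small downside, since the whole subgroup is scheduled for a pre-dose sample, and the number affected should be reported.

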## **6.11. Randomization and Blinding**

### **6.11.1. Randomization**

The randomization statistician will use SAS statistical software and generate randomization blind code with the method of "block randomization". After the investigator confirms that the participant is eligible for inclusion and signs the informed consent, the participant will be assigned a randomized study number (randomization number). The investigator will choose the investigational vaccine or placebo with the same number as the randomization number and give the injection to the participant. For the randomized participants who withdraw from the clinical study for any reason, regardless of whether they have been vaccinated with the investigational vaccines before, their randomization numbers will be retained and not be distributed again, and the participants will not be permitted to participate in this study.

Back-up vaccines: The block randomization method will be used to generate a randomization list of back-up vaccines, with a total of 320 vaccines (160 study

---

vaccines and 160 placebos). When the backup vaccine is used, the investigator should log into the back-up vaccine system to obtain the corresponding number of the back-up vaccine.

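### A paired t-test is specified to compare neutralizing-antibody GMT and GMI between two independently randomised arms that contain no pairs

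*Protocol*

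**What the plan says.** Protocol section 11.8.2.4 first sets the description: "The GMT and GMI of SARS-CoV-2 neutralizing antibodies in the test group and the control group in the immunogenicity subgroup will be statistically described", using the geometric mean and a two-sided 95% CI. The next sentence sets the test: "The paired t-test of the logarithmically transformed results will be used to perform statistical tests on the difference between the test group"; its closing words name the placebo arm as the comparator. The contrast is thus explicitly one arm against the other.

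The design behind that contrast is parallel-group. Under section 6.5.2 participants "will be 1:1 randomly assigned into the experimental group or the control group", and "the first 50 participants enrolled in each group (a total of 100 participants) will be set as the immunogenicity subgroup". Section 6.11.1 describes block randomisation and mentions no matching.

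For seroconversion in the same two groups, section 11.8.2.4 uses independent-sample methods, chi-square or Fisher's exact: "precision probability test will be used to compare the statistical differences in the positive conversion rates between the test group and the control group".

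**The concern.** A paired t-test analyses differences within defined pairs. Each observation needs a known partner: the same person at another time, or a matched person. Here each participant belongs to one arm only and has no partner in the other, so the analyst would have to invent the pairs. Different inventions give different p-values from the same data, and if the arms contribute different numbers there is no complete pairing.

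Section 6.2.2 lists neutralizing-antibody GMT and GMI as secondary endpoints at five post-vaccination times, and this is the only between-arm test the protocol states for them. At stake is whether those p-values can be produced and reproduced. Choosing a substitute after unblinding would be a post hoc decision.

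**Working it through.** **Inputs from the protocol.** 50 participants per arm (6.5.2); 1:1 parallel allocation (6.5.2); block randomisation without matching (6.11.1); paired t-test on log-transformed results for the between-arm difference (11.8.2.4). The protocol gives no sample size, power or titre variance for this comparison, so there is no stated figure to reproduce.

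**Assumptions, for illustration only.** Independent normal log10 titres, SD 0.5 in each arm, two-sided 5% level, true differences of 0, 0.2 and 0.3 log10.

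**1. Degrees of freedom.** Two-sample: 50 + 50 − 2 = 98, critical t 1.984. Paired: 50 − 1 = 49, critical t 2.010. The loss is small.

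**2. Long-run behaviour with equal numbers and arbitrary pairing (40,000 simulated trials per difference).**

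| True difference (log10) | Rejection rate, paired | Rejection rate, two-sample |
|---|---|---|
| 0 | 5.1% | 5.1% |
| 0.2 | 50.0% | 50.6% |
| 0.3 | 84.1% | 84.7% |

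The nominal level holds and the power loss is under one percentage point.

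**3. Dependence on ordering.** Take one fixed data set with observed difference 0.2 and SD 0.5 in each arm.

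- Two-sample: t = 0.2 / √(0.25/50 + 0.25/50) = 0.2 / 0.1 = 2.0 on 98 df, p = 0.048, however the rows are sorted.
- Paired: the variance of the differences is 0.25 + 0.25 − 2r(0.25) = 0.5(1 − r), where r is the sample correlation created by the chosen pairing. So t = 0.2 / √(0.5(1 − r)/50) = 2.0 / √(1 − r) on 49 df.
- Over random pairings r has mean 0 and SD 1/√49 = 0.143, so about 95% of pairings have r between −0.28 and +0.28.
- At r = +0.28: t = 2.0/√0.72 = 2.36, p about 0.022. At r = −0.28: t = 2.0/√1.28 = 1.77, p about 0.083.
- Simulation agrees: over 20,000 random pairings the central 95% of p-values is 0.023 to 0.083 and the full range is 0.005 to 0.112.

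One data set therefore falls on either side of 0.05 according to row order alone.

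**4. Unequal numbers.** With, for example, 48 and 45 evaluable participants, the paired statistic is undefined. Section 11.8.1 allows this: the immunogenicity per-protocol set (I-PPS) takes participants who "had blood samples collected at the evaluation time points, and had valid antibody data" and is defined separately for days 7, 14 and 28. The persistence set (IPS) works the same way at 3 and 6 months, and section 11.8.4 leaves missing persistence data as they are.

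**The case against.** The strongest defence is that this is a wording slip that does little harm. The English is visibly translated, the neighbouring seroconversion test is an independent-sample method for the same arms, and an independent-samples t-test was probably meant. The endpoints carry no hypothesis, power or success criterion, and involve 100 of about 3,200 participants. This bears on severity and stands there. It does not make the sentence right: the governing text names a specific test for a specific contrast, and the two do not fit.

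A second defence is that block randomisation supplies a natural pairing by enrolment order. The protocol gives no block size and defines no partner within a block.

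A reader might also infer more than the text supports:

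- **Inflated type I error or a material loss of power.** With equal numbers neither occurs (working, step 2).
- **Any missing sample breaks the test.** For the full analysis set (I-FAS), section 11.8.1 requires valid pre-vaccination antibody data and section 11.8.4 carries the last observation forward for missing post-vaccination results, so its numbers stay largely intact. The problem arises in I-PPS and IPS, or if I-FAS entry itself differs by arm.
- **All secondary GMT and GMI endpoints are affected.** The sentence covers neutralizing antibody only. Section 11.8.2.4 names no between-arm test for S-protein IgG, which may be left to the statistical analysis plan.
- **A before-and-after test within each arm is intended, so both arms could be significant without a vaccine effect.** The sentence says test group against control group, which excludes that reading.

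**Conclusion.** Wrong as written; moderate severity. The paired t-test does not apply to independent arms. With equal numbers it gives a p-value that depends on an arbitrary ordering; with unequal evaluable numbers it gives none.

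The reach is narrow: the p-values for the secondary neutralizing-antibody GMT and GMI comparisons. The primary VE analysis (Poisson regression, section 11.8.2.3) and the per-arm GMT and GMI with 95% CIs do not use this test.

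The conclusion about applicability rests on the design alone and needs no numerical assumption. The p-value range (0.005 to 0.112 around a two-sample 0.048) rests on the assumed SD of 0.5 and difference of 0.2 log10, chosen to lie near the 5% boundary; a large vaccine effect would be significant under almost any ordering.

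**What to change.** In section 11.8.2.4, replace the paired t-test for the between-arm comparison by one of:

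- a two-sample t-test on log-transformed titres (for GMT) and on log fold-rises from baseline (for GMI); this is the minimum correction; or
- ANCOVA of log titre on group and log baseline titre. This may gain precision, but the amount depends on the baseline correlation, which the protocol does not give.

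In either case report the between-arm GMT or GMI ratio with its 95% CI at each time point. Keep a paired t-test only for change from baseline within an arm, if that is wanted, and label it as such.

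The cost is one protocol sentence, to be settled before unblinding. Pre-vaccination blood is already drawn in the immunogenicity subgroup (sections 6.8 and 11.5), so no new data are needed and no sample size changes.
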